### Endpoint definitions

#### Primary outcome

Onset of one or more of predefined clinically significant adverse effects assessed as due to RAI during the 3-month period following completion of RAI treatment.

Side effects of RAI treatment will all be assessed clinically as there are no reliable tests to assess the side effects. The majority of the steroid-related side effects will also be assessed clinically, except capillary blood sugar level which will be assessed daily by the patient if on treatment for diabetes mellitus. Those without diabetes mellitus will not undergo routine capillary blood sugar monitoring as short-term, low-dose prednisolone does not warrant routine blood sugar monitoring in healthy individuals, in contrast to long-term administration [12]. The details and definitions of the adverse effects are given in Table 1. Clinically significant adverse effects are defined as the maximum severity of the adverse events assessed as related to RAI reaching the predefined level mentioned in Table 1 and/or if symptoms defined in Table 1 of any level of severity persisting for a prolonged (more than 2 weeks) duration.

**Table 1 Tab1:** Definition of clinically significant outcomes

Related to	Classification	Symptom	Definition	CTCAE grade and definition
RAI	Local	Neck pain	A disorder characterized by marked discomfort sensation in the neck area	Grade 2 (impairment of instrumental activities of daily living) and above
RAI	Local	Neck swelling	A disorder characterized by marked enlargement in the neck area	Grade 2 (impairment of instrumental ADL) and above
RAI	Local	Dysphagia	A disorder characterized by difficulty in swallowing	Grade 2 (symptomatic and altered eating/swallowing) and above
RAI	Local	Dyspnoea	A disorder characterized by difficulty in breathing	Any grade
RAI	Oral	Sialadenitis	A disorder characterized by an inflammatory process involving the salivary gland	Grade 2 (moderate symptoms; oral intervention indicated) and above
RAI	Oral	Dry mouth	A disorder characterized by reduced salivary flow in the oral cavity	Grade 2 (moderate symptoms; oral intake alterations; unstimulated saliva 0.1 to 0.2 mL/min)
RAI	Oral	Oral mucositis	A disorder characterized by inflammation of the oral mucosal	Grade 2 (moderate pain; not interfering with oral intake; modified diet indicated) and above
RAI	Oral	Oral pain	A disorder characterized by a sensation of marked discomfort in the mouth, tongue or lip	Grade 2 (moderate pain; limiting instrumental ADL) and above
RAI	Oral	Dysgeusia	A disorder characterized by abnormal sensual experience with the taste of foodstuffs	Grade 2 (altered taste with change in diet (e.g. oral supplements), noxious or unpleasant taste, loss of taste) and above
RAI	Gastrointestinal	Nausea	A disorder characterized by a queasy sensation and/or the urge to vomit	Grade 2 (oral intake decreased without significant weight loss, dehydration or malnutrition) and above
RAI	Gastrointestinal	Vomiting	A disorder characterized by the reflexive act of ejecting the contents of the stomach through the mouth	Grade 2 (3–5 episodes (separated by 5 min) in 24 h) and above
RAI/glucocorticoids	Gastrointestinal	Dyspepsia	A disorder characterized by an uncomfortable, often painful feeling in the stomach, resulting from impaired digestion. Symptoms include burning stomach, bloating, heartburn, nausea and vomiting	Grade 2 (moderate symptoms; medical intervention indicated) or above
RAI/glucocorticoids	Gastrointestinal	Abdominal pain	A disorder characterized by a sensation of marked discomfort in the abdominal region	Grade 2 (moderate pain; limiting instrumental ADL)
RAI	Eye	Xerophthalmia	A disorder characterized by dryness of the cornea and conjunctiva	Grade 2 (symptomatic; multiple agents indicated; limiting instrumental ADL) and above
RAI	Eye	Epiphoria	A disorder of excessive tearing in the eyes	Grade 2 (intervention indicated) and above
RAI	Eye	Conjunctivitis	A disorder characterized by inflammation, to the conjunctiva of the eye	Grade 2 (symptomatic; topical intervention indicated (e.g. antibiotics); limiting instrumental ADL) and above
Glucocorticoids	General	Infections within 2 weeks	A disorder characterized by an infectious process	Grade 2 (any infection that needs intervention) or above
Glucocorticoids	General	Hyperglycaemia during the first 3 days	A disorder characterized by laboratory test results that indicate an elevation in the concentration of blood sugar	Grade 3 (> 250–500 mg/dL; > 13.9–27.8 mmol/L; hospitalization indicated) or above
Glucocorticoids	Central nervous system	Altered sensorium	A disorder characterized by functional disturbances of sensory neurons resulting in abnormal cutaneous sensations of tingling, numbness, pressure, cold and warmth that are experienced in the absence of a stimulus	Grade 2 (moderate symptoms limiting instrumental ADL) and above
Glucocorticoids	Central nervous system	Sleep disturbances	A disorder characterized by excessive or reduced sleepiness or difference in sleep pattern	Grade 2 (moderate disturbance) or above
Glucocorticoids	Central nervous system	Mood changes	A disorder characterized by a state of restlessness, irritability or sadness	Grade 3 (moderate symptoms; hospitalization not indicated) or above

*ADL* activities of daily living, *CTCAE* Common Terminology Criteria for Adverse Effects version 4.0

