Benefits to subjects will be directly related to the reduction of adverse effects of RAI provided that glucocorticoids are efficacious in reducing such effects. If the glucocorticoids are proven effective, this prophylactic measure could be incorporated to routine practice to minimize adverse effects of RAI. Potential risks would include potential adverse effects of short course of glucocorticoids; however, proton pump inhibitors will be concurrently administered to minimize gastrointestinal adverse effects. Other rare adverse effects include transient increased susceptibility to infections, transient hyperglycaemia, sleep disturbances, altered sensorium and mood changes. In the event of adverse effects to the subjects, medical or professional intervention will be sought. All participants will be educated about the adverse effects of RAI and the safety precautions that should be taken after administration.

If proven to be effective, short-term steroid prophylaxis could be made standard with the administration of RAI treatment for differentiated thyroid cancer which would minimize side effects and improve quality of life.

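### Table 1 contains outcome definitions that contradict themselves or the assessment plan (altered sensorium, mood changes, hyperglycaemia and, less importantly, dry mouth) and should be reconciled before recruitment

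*Protocol article*

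**What the plan says.** All references are to the protocol article. Table 1, under Primary outcome, gives each adverse effect a definition and a CTCAE level from which it counts as clinically significant. Some rows concern radioactive iodine (RAI), some glucocorticoids, and two concern both.

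- **Altered sensorium** (glucocorticoids, central nervous system) is defined by "functional disturbances of sensory neurons resulting in abnormal cutaneous sensations of tingling, numbness, pressure, cold and warmth". The Discussion places the same term in a list of steroid effects: "transient hyperglycaemia, sleep disturbances, altered sensorium and mood changes".
- **Mood changes** (glucocorticoids) counts from "Grade 3 (moderate symptoms; hospitalization not indicated) or above". The two rows just above it read "Grade 2 (moderate disturbance) or above" (sleep disturbances) and "Grade 2 (moderate symptoms limiting instrumental ADL) and above" (altered sensorium).
- **Hyperglycaemia** (glucocorticoids, first 3 days) is defined by laboratory results and counts from Grade 3. The text before the table has patients on diabetes treatment check their own capillary glucose daily, and adds: "Those without diabetes mellitus will not undergo routine capillary blood sugar monitoring".
- **Dry mouth** (RAI) has the level "Grade 2 (moderate symptoms; oral intake alterations; unstimulated saliva 0.1 to 0.2 mL/min", closed without *and above*. The same section states: "Side effects of RAI treatment will all be assessed clinically as there are no reliable tests to assess the side effects". The section on protocol waivers and deviations says that no biological specimens are collected.

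**The concern.** Table 1 is the rule book for classifying events, so a row that disagrees with itself or with the planned assessments leads assessors to classify the same patient differently. Glucocorticoid-related adverse effects are a stated secondary objective and endpoint, and the argument for adopting prophylaxis rests partly on few steroid harms. At stake is whether the clinically significant steroid events can be compared and interpreted as labelled, and whether a low hyperglycaemia count could be taken as evidence of safety in patients whose glucose was not routinely measured. The dry mouth row matters less, but it feeds the primary endpoint.

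**Working it through.** **The plan's own figure.** The sample size is not in dispute. With 20% vs 10%, two-sided 5% alpha and 80% power:

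n = [1.960·√(2·0.15·0.85) + 0.842·√(0.20·0.80 + 0.10·0.90)]² / 0.10² = (0.990 + 0.421)² / 0.01 ≈ 199 per arm.

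The plan states 200, at which power is 80.2%. Nothing below changes this.

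**(a) Altered sensorium.** The term, the body-system heading and the Discussion list (next to sleep and mood) suggest a mental-state effect. The definition describes abnormal skin sensation. Applied literally, a confused patient without skin symptoms fails the row. A patient with tingling that limits instrumental daily activities, and that is judged steroid-related, passes it.

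**(b) Mood changes.** The rows whose level uses the word moderate are:

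| Row | Grade |
|---|---|
| Sialadenitis, dry mouth, oral mucositis, oral pain | 2 |
| Dyspepsia, abdominal pain | 2 |
| Altered sensorium, sleep disturbances | 2 |
| Mood changes | 3 |

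Eight rows equate moderate with Grade 2 and one with Grade 3. A patient whose worst mood symptoms are moderate counts if the descriptor is followed. If the number is followed, and moderate means Grade 2 as elsewhere in the table, the same patient does not count. The documents give no rate for such patients, so the number affected cannot be stated.

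**(c) Hyperglycaemia.** The event needs a glucose reading in the first 3 days. During that time patients are in isolation for 3–5 days and followed by phone, and the first visit is at 2 weeks. Routine readings therefore come only from patients treated for diabetes, and uncontrolled diabetes is an exclusion. Let s be the share treated for diabetes (not in the documents; assumed 5–20%), r_m the event rate in monitored patients and r_u the rate in the others.

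- Monitored per arm: 200·s.
- If only monitored patients' events are seen and all patients form the denominator, the reported rate is s·r_m.
- The true all-patient rate is s·r_m + (1−s)·r_u.
- True rate / reported rate = 1 + [(1−s)/s]·(r_u/r_m). This is 1 if r_u = 0, and 1/s if r_u = r_m.

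As an illustration of information content only, the last three columns give the chance 1−(1−r)^m of seeing at least one event among the m monitored patients in an arm, for an assumed rate r that is the same in everyone:

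| s (assumed) | m per arm | 1/s | r = 1% | r = 2% | r = 5% |
|---|---|---|---|---|---|
| 5% | 10 | 20 | 10% | 18% | 40% |
| 10% | 20 | 10 | 18% | 33% | 64% |
| 20% | 40 | 5 | 33% | 55% | 87% |
| all monitored | 200 | 1 | 87% | 98% | 100% |

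**(d) Dry mouth and abdominal pain.** The flow range has no source of data: RAI effects are assessed clinically, no specimens are taken, and visits consist of history, examination and questionnaires. The symptom and oral-intake parts of the row can still be graded. Of the 20 rows with a numbered grade (dyspnoea is any grade), 18 say *and above* or *or above*. Only dry mouth and abdominal pain do not.

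**The case against.** The strongest reply is that much of this is caught elsewhere, and several parts of it stand.

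- **Missed cases.** A reader might infer that confusion or moderate mood change would be lost. The documents do not support that. The secondary objective covers all adverse effects related to glucocorticoids, the endpoint for them is not confined to Table 1, and all adverse events are recorded and graded. What goes wrong is the clinically significant label.
- **Tingling after thyroidectomy.** A reader might infer that it would be logged as a steroid effect. Events must be assessed as related, symptoms are analysed at baseline, and the row requires limitation of instrumental daily activities. Such cases would also be expected in both arms of a blinded randomized trial.
- **Mood changes.** The number is explicit and CTCAE version 4.0 is the named scale, so an assessor could follow the number. The descriptor still contradicts it.
- **Glucose.** Limited monitoring is a deliberate choice with a stated reason; only routine testing is omitted. Nothing says that untested patients count as event-free, and a denominator may be set in an analysis plan that is not shown. The conflict between a laboratory-defined outcome and who is routinely measured nevertheless stands in the text.
- **Dry mouth.** The row remains gradeable. Significance is defined by maximum severity reaching the tabled level, so a higher grade passes, and any grade lasting more than 2 weeks also counts. The missing *and above* is therefore close to editorial.

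**Conclusion.** The inconsistencies are real and should be corrected before recruitment, but their reach is limited. Parts (a) to (c) affect the clinically significant classification within a secondary safety endpoint. Only (d) touches the primary endpoint, and its effect is small. Power and the primary analysis method are unaffected.

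Two stronger readings should be resisted. One is that these rows cannot measure what they name. That fits altered sensorium, and hyperglycaemia in patients who are not monitored; mood changes has an ambiguous threshold, and dry mouth has one unusable criterion.

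The other is that the hyperglycaemia rate would be understated 5- to 10-fold. With 10–20% of patients treated for diabetes, that factor is 1/s. It holds for all patients only if those without diabetes cross the threshold as often as those with it, which nothing in the documents supports. If they never do, there is no understatement. The diabetes share is also not given. What can be said is that a low count would carry little information about unmonitored patients.

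**What to change.** 1. **Altered sensorium:** make the term and the definition agree. The documents do not settle which was intended, so the investigators must decide.
2. **Mood changes:** reconcile the grade number with its descriptor.
3. **Hyperglycaemia:** report incidence by arm with glucose-monitored patients as the denominator, show that denominator, and draw no safety conclusion for unmonitored patients.
4. **Dry mouth and abdominal pain:** drop the saliva flow figure from the operational dry mouth threshold, and add *and above* to both rows for consistency with the definition of clinical significance.

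The cost is edits to Table 1 and the case form, one denominator, and the ethics committee approval that the protocol requires for amendments. No extra tests or patients are needed. Trial status says that recruitment had not begun, so the edits can be in place before any patient is graded.

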#### Secondary endpoints

Onset of any type, grade and duration of early and intermediate adverse effects assessed as due to RAIOnset, duration, recurrence and severity (CTCAE) of early and intermediate adverse effects of RAI defined in Table 1Onset, incidence, severity, duration and type of adverse events assessed in relation to glucocorticoidsPatient-reported outcomes related to adverse effects of RAI and glucocorticoids: NCI PRO-CTCAE at 2 weeks and 3 months after completion of RAIQuality of life scores: EQ-5D-5L and FACT H&N

(CTCAE Common Terminology Criteria for Adverse Effects, PRO-CTCAE Patient-Reported Outcomes-Common Terminology Criteria for Adverse Effects version 4.0, FACT H&N Functional Assessment of Cancer Therapy Head and Neck)

### Screening evaluation

Those who fulfil the eligibility criteria will be invited to participate in the study.Clinical examination will include that of oral examination and eye examination to look for evidence of prior diseases similar to the adverse effects mentioned in Table 1.Full blood count will be done in all patients to confirm eligibility.Studies will be completed within 4 weeks prior to enrolling onto the protocol.

### Registration procedures

All patients will be registered on study once study consent has been obtained and eligibility has been confirmed by the investigators. Registration and randomization will be performed 2 weeks prior to the planned date of RAI.

#### Randomization (or stratification) procedures

At study entry, patients will be randomly allocated to one of the two arms, the intervention arm and the placebo arm. Randomization will be balanced (1:1), using permuted blocks, and stratified according to the total dose of RAI given for stratification into three groups. Criteria for stratification will be 50–100, > 100 and < 200, and > 200 mCi.An independent investigator will be responsible for randomization of treatment using an online randomization software, ensuring concealment of treatment allocation for the next patient.

#### Baseline evaluation

Clinical assessment: Symptom analysis and oral and eye examinationEQ-5D-5L and FACT H&NThese will be completed within 2 weeks before the first dose of drug or registration.

#### Drug administration

The treatment group will receive oral prednisolone 0.5 mg/kg and omeprazole 20 mg single dose 6 h before RAI therapy and followed by prednisolone 0.5 mg/kg and omeprazole 20 mg daily for 3 days. The control group will receive oral placebo and omeprazole 20 mg single dose 6 h before RAI therapy and followed by placebo and omeprazole 20 mg daily for 3 days.

### Follow-up procedures

All patients will be given a symptom diary and instructions will be given how to maintain it. Patients will be instructed to bring the diary at each follow-up visit through telephone reminders. If they develop a problematic adverse effect, they will be instructed to contact the investigator. During visit 1 at 2 weeks, clinical interviews will be conducted to assess the adverse effects including oral and eye examination. The adverse effects will be recorded based on the CTCAE grading system by the investigator and also by patient-reported outcome measures NCI PRO-CTCAE. The patients will be reminded about the follow-up visits by phone calls. Data on patients who discontinue the trial or deviate from the protocol will be recorded.

The quality of life instruments including EQ-5D-5L and FACT H&N will be completed by the patient. During visit 2 at 3 months, the same assessment will be conducted with more emphasis on the intermediate adverse effects.

Criteria for removal from protocol therapy include participant requests to be withdrawn from therapy and unacceptable toxicity such as infections, hyperglycaemia or severe dyspepsia. Furthermore, a patient who would prematurely stop the treatment will not be withdrawn from the study unless he/she requests to be withdrawn from the study. There are no specific concomitant treatments or interventions that are permitted or prohibited during the trial.

Off-study criteria include completed 3-month follow-up period, subject withdrawal from the follow-up period and death.

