### Exclusion criteria

Those with absolute and relative contraindications for glucocorticoids such as uncontrolled diabetes mellitus, gastric and duodenal ulcers, immunosuppression, ongoing or active infections and chronic infective diseasesHistory of previous RAI therapyPrevious major head and neck surgeryPatients with previous history of salivary gland diseases, such as sialadenitis, duct obstruction and calculi, and ophthalmological diseases such as xerophthalmia and conjunctivitisUncontrolled concurrent illness including, but not limited to, symptomatic congestive heart failure, unstable angina pectoris, cardiac arrhythmia or psychiatric illness/social situations (within 12 months before the study) that would limit compliance with study requirements.Pregnant women and breast-feeding mothers are excluded as RAI therapy is contraindicated in such patientsDiagnosed HIV-positive patients on combination antiretroviral therapy are ineligible as glucocorticoids may further suppress the immunity and increase the chances of opportunistic infectionPrior diagnosis of cancer that was:
More than 5 years prior to current diagnosis with subsequent evidence of disease recurrence or clinical expectation of recurrence is greater than 10%Within 5 years of current diagnosis with the exception of successfully treated basal cell or squamous cell skin carcinoma or carcinoma in situ of the cervix

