### Study assessments

Participants will be given an information sheet and will be explained in detail about the study, and informed written consent will be taken prior to recruitment. The basic demographic information including age, sex, ethnicity and medical history including the details related to thyroid cancer (such as type, grade, stage, lymph node involvement), comorbidities and the current treatment will be collected using the clinic notes and interviewer-administered questionnaire. The contact details will also be collected for the purpose of follow-up. A general physical examination will be performed for a baseline assessment prior to administration of RAI. Basic haematological parameters including full blood count and renal functions will be performed before RAI treatment. A baseline quality of life scores which are EQ-5D-5L and FACT H&N will be measured [10]. Data collection tool is attached in the Supplementary file.

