Patients will be stratified based on the dose of the RAI into three strata (50–100, > 100 and < 200, and > 200 mCi) based on the American Thyroid Association Guidelines 2015 [11]. From each group, patients will be randomized to two arms, the experimental and the placebo arms. All patients will be given a diary and asked to keep a log of any new symptoms after RAI therapy. Patients in both groups will be instructed to have sugar-free hard candy or gum in their mouths at all times when awake for a period of 1 week. Proton pump inhibitors are routine given in our setting to minimize dyspeptic symptoms which are reported to occur in around 50% and thus will be given to both arms [5]. This will also be helpful to minimize the gastrointestinal adverse effects of glucocorticoids. At least a fluid input of 2400 mL will be maintained during the first week after therapy. If a patient develops adverse effects of RAI, symptomatic management would be given, and the given treatment will be documented. Each patient will be reviewed at 2 weeks and 3 months by history, examination to assess for abovementioned side effects, for the measurement of quality of life scales and for possible complications of glucocorticoids. The onset, duration, recurrence and rate of each early and intermediate adverse effect will be assessed by a clinical interview and examination. For the grading of severity of the adverse effects, the Common Terminology Criteria for Adverse Effects version 4.0 will be used for an objective assessment by the clinician. Furthermore, the Patient-Reported Outcome version of the Common Terminology Criteria for Adverse Effects questionnaire will also be used to get the patient’s perspective regarding the presence of symptoms and their severity. After the study has been completed, patients will be subjected to standard routine follow-up for thyroid cancer.

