### Statistical analysis

Analyses will be performed in accordance with the intention-to-treat analysis principle.

All randomized participants randomized to study and control groups will be included in the main analyses irrespective of protocol adherence (i.e. intention-to-treat analysis). An additional per-protocol analysis will also be conducted only including the patients who adhered to the treatment protocol with completed follow-up. For each patient, the maximum grade for all types of events will be calculated over the whole observation period. The maximum grades per patient will be tabulated, first considering all adverse effects, then focusing on clinically relevant adverse effects as defined in Table 1 (primary endpoint). The proportion of patients who have experienced clinically relevant adverse effects will be estimated in each group. Difference of proportions between the 2 treatment groups as well as odds ratio will be provided to estimate the impact of glucocorticoids on the risk of clinically significant RAI therapy-related adverse effects. All these estimates will be provided with their 95% confidence intervals. Analyses will be adjusted on the stratification factors. Comparisons between groups on binary endpoints will be performed using a logistic regression, and comparisons between groups on continuous endpoints will be performed using *t* tests. The *p* value will be evaluated at the 5% level of significance. No adjustment will be made for multiple comparisons associated with secondary analyses, but these will be evaluated in proper context and fully reported.

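### Non-study prophylactic glucocorticoid is not barred in the placebo arm, which could slightly dilute the primary comparison toward no difference

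*Protocol article*

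**What the plan says.** On background treatment, Follow-up procedures takes a position: "There are no specific concomitant treatments or interventions that are permitted or prohibited during the trial".

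The glucocorticoid item in Exclusion criteria reads, in part: "Those with absolute and relative contraindications for glucocorticoids such as uncontrolled diabetes mellitus, gastric and duodenal ulcers, immunosuppression, ongoing or active infections". The list is open and includes immunosuppression, so some chronic steroid users may already be excluded. Neither the inclusion nor the exclusion criteria name current systemic glucocorticoid use.

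On recording, Study assessments says of the baseline interview that "comorbidities and the current treatment will be collected using the clinic notes and interviewer-administered questionnaire", and of later events: "If a patient develops adverse effects of RAI, symptomatic management would be given, and the given treatment will be documented". On timing, Registration procedures says: "Registration and randomization will be performed 2 weeks prior to the planned date of RAI".

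The primary outcome is "Onset of one or more of predefined clinically significant adverse effects assessed as due to RAI" over 3 months. An event counts if it reaches the Table 1 grade, or by a second route: "symptoms defined in Table 1 of any level of severity persisting for a prolonged (more than 2 weeks) duration".

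The main analysis is by intention to treat. Beside it, Statistical analysis says: "An additional per-protocol analysis will also be conducted only including the patients who adhered to the treatment protocol with completed follow-up".

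**The concern.** The comparison is informative only if the placebo arm goes largely without the drug class under test. Here that class is left unrestricted. Non-study steroid could reach a placebo patient before a primary event in two ways:

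- **Prophylaxis around RAI**, including steroid antiemetics or steroid the patient already takes at registration.
- **Early treatment of a symptom** still below the Table 1 grade. This could stop the symptom reaching that grade, or end it before it has lasted more than 2 weeks.

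Either could prevent a primary event in the placebo arm. Intention to treat rightly keeps such patients where they were randomized, so the observed difference would shrink. What is at stake is some power and possibly a missed benefit. Steroid started after a qualifying event changes nothing in the primary endpoint, because that endpoint is onset.

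Recording covers only part of this exposure. Baseline treatment and treatment given for adverse effects are captured. Steroid given as prophylaxis in the 2 weeks between registration and RAI, or around the RAI dose, is named in neither provision.

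**Working it through.** **Inputs from Sample size calculation:** placebo rate 20%, prednisolone rate 10%, two-sided 5% alpha, 200 per arm, 80% power. **Assumed, because the article gives no figure:** the share s of placebo patients who receive non-study glucocorticoid, and the fraction b of the prednisolone benefit that they obtain.

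**Formula** (two proportions, pooled variance under the null, no continuity correction), with pC and pT the two rates and p̄ their mean:

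power = Φ{ [ |pC − pT|·√n − 1.96·√(2p̄(1 − p̄)) ] / √( pC(1 − pC) + pT(1 − pT) ) }

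**Step 1: reproduce the plan.** With pC = 0.20, pT = 0.10 and p̄ = 0.15:

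- 0.10 × √200 = 1.4142
- 1.96 × √(2 × 0.15 × 0.85) = 0.9897
- √(0.16 + 0.09) = 0.5
- (1.4142 − 0.9897)/0.5 = 0.849, so power = 80.2%

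The size needed for 80% power is (0.9897 + 0.8416 × 0.5)²/0.10² = 198.96, that is 199 per arm. The planned 200 reproduces, with one patient per arm to spare.

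**Step 2: dilute the placebo rate.** Set pC = 0.20 − s × 0.10 × b. Keep pT = 0.10, so that non-study steroid adds nothing in the prednisolone arm. For s = 5% and b = 1, pC = 0.195 and p̄ = 0.1475. The numerator is 0.095 × √200 − 1.96 × √(2 × 0.1475 × 0.8525) = 1.3435 − 0.9829 = 0.3606. The denominator is √(0.156975 + 0.09) = 0.4970. The ratio is 0.726 and power is 76.6%.

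| Share s (patients of 200) | pC, full benefit | Power, full benefit | n per arm for 80% | Power, half benefit |
|---|---|---|---|---|
| 0 | 20.0% | 80.2% | 199 | 80.2% |
| 1% (2) | 19.9% | 79.5% | 203 | 79.9% |
| 2% (4) | 19.8% | 78.8% | 207 | 79.5% |
| 5% (10) | 19.5% | 76.6% | 218 | 78.4% |

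The loss runs from 80.2 − 79.9 = 0.3 points to 80.2 − 76.6 = 3.6 points. The half-benefit column suits later or shorter courses. Many of those would be rescue treatment, so it should not be read as power that a ban on prophylaxis would recover.

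**Step 3: is such use a deviation?** The dosing section and Drug administration fix each arm's regimen, and the control regimen is placebo with omeprazole. Follow-up procedures prohibits nothing in addition to it. On the first text, steroid prophylaxis in a control patient departs from the regimen. On the second, that patient took every study dose and broke no rule. The per-protocol definition turns on adherence to the treatment protocol and does not say which reading applies.

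**The case against.** **No exposure is documented.** No section says that patients at this centre receive steroid around RAI outside the trial. Study assessments lists a proton pump inhibitor, sugar-free candy or gum, and fluids. A reader might infer routine use from the Study rationale, which says that practice varies, but that remark concerns management of adverse effects and not prophylaxis. The prophylactic indication in the Discussion (deposits near vital structures or in confined spaces) is a literature statement. Eligibility (total thyroidectomy, ECOG 0–1, no earlier RAI or radiotherapy) probably leaves few such patients, and a clinician who thought cover necessary would be unlikely to enrol them. This stands. It is why the assumed range stops at 5% and why larger shares have no basis in the article.

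**Blinding and randomization limit the harm.** Non-study prophylaxis would be given without regard to arm, and any extra benefit in the prednisolone arm would reduce the dilution. This also stands, and the calculation is the less favourable case. Balance between arms does not remove the dilution, however, because a placebo patient on steroid is still exposed to the tested class.

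**Unrestricted background care with intention to treat is a legitimate pragmatic choice.** True in general, and the bias is conservative. It fits less well when the unrestricted treatment is the one under test.

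**Stronger readings to avoid.** A reader might infer that steroid in the placebo arm is expressly allowed, can never be a deviation, and would therefore survive the per-protocol analysis. The sentence in Follow-up procedures is neutral, neither permitting nor prohibiting, while the regimen of each arm is fixed elsewhere. The text supports only that the status is unclear. A reader might also infer that a ban would cure the whole problem. It would not, because rescue for symptoms below the Table 1 grade has to remain available.

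**Conclusion.** The concern holds as a minor design point. The article prohibits no concomitant treatment and does not exclude current systemic glucocorticoid users as such, so non-study prophylaxis with the tested drug class is not barred in the placebo arm. If it occurs, it dilutes the intention-to-treat comparison toward no difference.

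The size rests on assumed exposure. With fully effective prophylaxis in 1% to 5% of placebo patients, and no added effect in the prednisolone arm, power falls by 0.7 to 3.6 points. Actual use is probably at the low end. The design has almost no reserve, so even slight dilution takes power below the stated 80%, though not by much. The risk is a missed benefit. The text does not support a claim that the result is invalid or that a false positive becomes more likely.

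**What to change.** Replace the sentence in Follow-up procedures with wording such as: *Systemic glucocorticoids other than study drug, including steroid antiemetics, are not to be given as prophylaxis around RAI, and such use is a protocol deviation. Therapeutic rescue is allowed when clinically needed; its date, its reason and the CTCAE grade at its start are recorded.* Add to Exclusion criteria: *systemic glucocorticoid use at registration.*

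Keep the primary endpoint, the sample size and the intention-to-treat analysis as they are. Examine rescue steroid in a sensitivity analysis only. This shows how often early rescue for sub-threshold symptoms occurred and in which arm, but does not undo its dilution.

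The cost is two short text changes and a small extension of what is already recorded, made before the recruitment start anticipated under Trial status. The trade-off is that patients judged to need steroid prophylaxis are not randomized, a small loss of applicability in a group for whom placebo would be hard to justify.
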